### 2.5 Intervention

Participants will be randomly categorized into two parallel groups to undergo acupuncture at acupoints on the DAM or non-acupoints on the NAM for 8 weeks (every 2^nd^ day, three times a week). The six standardized acupoints on the DAM are as follows: (1) EX-B1 (Dingchuan), (2) BL13 (Feishu), (3) BL20 (Pishu), (4) BL23 (Shenshu), (5) LU7 (Lieque), and (6) ST36 (Zusanli) (Table 2). The six non-acupoints on the NAM have been designed to be 2.0 cun away from the acupoints on the DAM listed above (Figure 3). Acupuncture will be performed on patients in the prone position, using disposable stainless-steel needles inserted into the disinfected skin. The locations, directions, and depths of needle insertion are presented in Table 2. Minor stimulation, achieved by lifting and thrusting the needles along with thrusting and rotating the needle sheath, will be applied to produce the sensation known as deqi (a feeling of soreness, numbness, distention, or radiation, which is considered effective). Acupuncture needles will be inserted at the intended acupoints for 30 min.

**Table 2 T2:** Location of acupoints on the disease-affected meridian.

**Acupoints**	**Location**	**Depth**	**Direction**
Dingchuan (EX-B1)	On the back of the neck, 0.5 cun apart from the midpoint of the lower edge of the spinous process of the seventh cervical vertebra	0.5–1.0 cun	Vertically puncture or the needle point toward the spine
Feishu (BL13)	On the back, 1.5 cun apart from the spinous process of the third thoracic vertebra	0.5–0.8 cun	Oblique puncture
Pishu (BL20)	On the back, 1.5 cun apart from the spinous process of the eleventh thoracic vertebra	0.5–0.8 cun	Oblique puncture
Shenshu (BL23)	1.5 cun apart from the spinous process of the second lumbar vertebra	0.5–1.0 cun	Vertically puncture
Lieque (LU7)	On the radial side of the forearm and above the radial styloid process, between the brachioradialis muscle and the abductor pollicis longus tendon, 1.5 cun above wrist crease	0.2–0.3 cun	Upward oblique puncture
Zusanli (ST36)	On the outside of the shank, 3 cun below Dubi^*^ and a thumb lateral to the anterior tibial ridge	1.0–2.0 cun	Vertically puncture

^*^Dubi (ST35): when the knee is bent at a right angle, the acupoint is located at the concave position on the outer side of the patellar ligament of the knee joint.

**Figure 3 F3:**
[figure not shown]
Location of acupoints or the non-acupoints on the disease-affected or non-affected meridian in the trial. The red dots are the acupoints used on the disease-affected meridian (DAM) and the green dots are the non-acupoints on the non-affected meridian (NAM).

### 2.6 Outcome measurement

All outcomes will be measured at baseline and after 8 weeks of intervention treatment.

#### 2.6.1 Primary outcomes

The primary outcome is the severity of dyspnea measured after the 6-min walking test (6MWT). The severity of dyspnea at rest and exertional dyspnea after 6MWT will be assessed using the Borg Dyspnea Scale and a VAS, which are convenient, simple to use, and often used for measuring exertional dyspnea; scores will be recorded within 1 min of finishing the 6MWT.

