**Methods:**

This is a prospective, multicenter, single-blind, randomized controlled trial. A total of 90 participants will be recruited from three centers and will be randomly assigned in a 1:1 ratio to undergo acupuncture at acupoints on the disease-affected meridian (DAM) or non-acupoints on the non-affected meridian (NAM), in addition to routine pharmacological treatments. All participants will undergo 30 min of acupuncture three times a week for 8 weeks and will be followed up for 12 months. The primary outcome will be the severity of dyspnea, as measured using the Borg Dyspnea Scale and a visual analog scale at rest and after exercise. The secondary outcomes will include the multidimensional profile of dyspnea using Dyspnea-12, the modified Medical Research Council Dyspnea Scale, and the COPD assessment test; quality of life assessments using St George's Respiratory Questionnaire and the Hospital Anxiety and Depression Scale; and additional measurements of exacerbation frequency, pulmonary function, and the 6-min walking distance. Magnetic resonance imaging (MRI) will be performed before and after exercise to explore the potential neurobiological mechanisms of exertional dyspnea. Anxiety and depression will be measured and analyzed for their correlation with the activation of specific brain areas involved in dyspnea.

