### 2.4 Sample size

The sample size calculation was based on the dyspnea visual analog scale (VAS) score, as reported by Liu et al. (29). The test for paired means in PASS software version 15.0.5 (NCSS Statistical Software, Kaysville, UT, USA) was used to calculate the dyspnea VAS score differences in the placebo and acupuncture groups before and after acupuncture, which determined that a total of 78 patients with stable COPD should be included in the study to achieve a statistical power of 0.95 and a significance level of 5% for difference detection. Assuming a dropout rate of 15% established the necessity of a sample size of 45 participants per group. The sample size calculation based on the Borg Dyspnea Scale, as reported by Li et al. (30), showed that a total of 16 patients with stable COPD should be included in the study to achieve a statistical power of 0.97 and a significance level of 5% for difference detection. Assuming a dropout rate of 20%, a sample size of 10 participants per group is required. This study, being a multicenter, clinical, randomized controlled trial, requires a larger sample size. Therefore, a sample size of 90 participants is considered to be reasonable for this study.

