### 2.8 Statistical analysis

Qualitative variables will be expressed as numbers (percentages), and quantitative variables will be expressed as mean (standard deviation) or median (interquartile range [25%−75%], q1–q3). All efficacy evaluation data will be summarized according to the full analysis set and the per-protocol set. For safety analysis, the safety set will include all randomized participants who received at least one interventional treatment. A paired *t*-test or Wilcoxon signed-rank test will be conducted to compare the outcomes at baseline with those after the 8-week intervention period and during follow-up within a group. Analysis of covariance will be performed to compare the results after acupuncture and during follow-up between the groups. Exercise intensity will be adjusted to assess post-exercise dyspnea. Data will be analyzed using SPSS software version 26.0 (IBM Corporation, Armonk, NY, USA), and statistical significance will be set as a *p*-value of < 0.05.

Metadata from DICOM files will be converted to BIDS using HeuDiConv. fMRIPrep software version 21.0.4, a combination of tools from common software packages including FSL, ANTs, FreeSurfer, and AFNI, was developed by the laboratory of Russ Poldrack and the Stanford Center for Reproducible Neuroscience and will be used to perform minimal data preprocessing, including skull stripping, motion correction, segmentation, co-registration, and normalization. Motion artifacts will be removed automatically using independent component analysis (40). Subsequently, graph theory-based or data-driven approaches will be used to compare the differences between the DAM and NAM groups.

PANDA, a MATLAB toolbox that can be downloaded from https://www.nitrc.org/projects/panda/ and is based on MATLAB R2016a in the Ubuntu 16.04 operating system, will be used to analyze brain diffusion images. The coupling value between the functional connection matrix and the structural joint matrix will be calculated and correlated with clinical symptoms.

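### The primary outcome is two scores or four depending on which sentence is read, and the article does not say which score decides the trial

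*Protocol article*

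**What the plan says.** The primary outcome is described in three places in the protocol article.

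- **Abstract, Methods:** the primary outcome is dyspnea severity, "as measured using the Borg Dyspnea Scale and a visual analog scale at rest and after exercise". Two scales in two states make four scores.
- **Section 2.6.1, first sentence:** "The primary outcome is the severity of dyspnea measured after the 6-min walking test (6MWT"). This covers the post-exercise state only, hence two scores if both scales count.
- **Section 2.6.1, second sentence:** "The severity of dyspnea at rest and exertional dyspnea after 6MWT will be assessed using the Borg Dyspnea Scale and a VAS". Rest is back, and there are four scores again.

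The heading of 2.6.1 is plural ("Primary outcomes") while its first sentence is singular. Borg and VAS then follow as parallel subsections, 2.6.1.1 and 2.6.1.2, with neither ranked first.

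Section 2.4 sizes the trial twice. The VAS calculation needs 78 patients "to achieve a statistical power of 0.95 and a significance level of 5% for difference detection"; the Borg calculation needs 16 "to achieve a statistical power of 0.97 and a significance level of 5% for difference detection". Neither says whether the score is at rest or after exercise. Section 2.8 plans analysis of covariance between groups and gives one general rule: "statistical significance will be set as a *p*-value of < 0.05".

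The time point is not in doubt. Section 2.6 and Table 1 place Borg and VAS at baseline and week 8 only.

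**The concern.** Which endpoint is primary is something the article does state, and it states it in two incompatible ways. Suppose post-exercise VAS shows no difference but resting Borg gives p = 0.04. The Abstract would allow that to be reported as a positive primary result; the first sentence of 2.6.1 would not. With no deciding score named, a mixed result has no agreed reading. Whether the trial's 5% error rate and its stated power apply to its main conclusion depends on a choice the text leaves open.

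**Working it through.** **Inputs.** Significance level 5% (2.4 and 2.8; two-sided assumed, as sidedness is not stated). VAS calculation: 78 patients, power 0.95, 15% dropout. Borg calculation: 16 patients, power 0.97, 20% dropout. Number of primary scores: 2 or 4. Correlations between scores are not given, so a range is assumed.

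**Step 1: the plan's own figures.**
- One test at 0.05: 1 − (1 − 0.05) = 0.05. The stated 5% is right for one test.
- VAS: 78 × 1.15 = 89.7, rounded to 90, or 45 per group as stated. (Dividing instead, 78 / 0.85 = 91.8, gives 92.)
- Borg: 16 / 0.80 = 20, or 10 per group as stated.
- The bases of 78 and 16 cannot be re-derived, because no effect size or standard deviation is given.
- The total of 90 therefore follows from the VAS calculation, not the Borg one.

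**Step 2: error rate if any one significant score counts.** With k independent scores the rate is 1 − 0.95^k: for k = 2, 1 − 0.9025 = 9.75%; for k = 4, 1 − 0.8145 = 18.5%. For correlated scores, two-sided normal tests with a common correlation were simulated (2,000,000 draws):

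| Assumed correlation | Any one of 2 | Any one of 4 |
|---|---|---|
| 0 | 9.75% | 18.5% |
| 0.5 | 9.1% | 15.6% |
| 0.7 | 8.4% | 13.0% |
| 0.8 | 7.8% | 11.4% |
| 0.9 | 7.0% | 9.4% |

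Relative to 5%, that is 1.4 to 1.95 times for two scores and 1.9 to 3.7 times for four. A more structured assumption for four scores (correlation 0.6-0.9 between scales, 0.3-0.6 between rest and exercise) gives 12.1-16.4%, or 2.4 to 3.3 times.

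**Step 3: error rate if all must be significant.** Joint success requires every test to pass at 0.05, so the rate cannot exceed 5%. With no effect on any score, the simulation gives 1.9% or less for four scores at correlations up to 0.9, and 3.0% for two scores at 0.9.

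**Step 4: power if all must be significant.** The stated powers are for one scale each. If both held in the same analysed sample, the chance that both scales succeed lies between 0.95 + 0.97 − 1 = 0.92 and 0.95. Because 0.97 was stated for only 16 patients, the Borg assumptions would give more at 78, so the loss for two scores may be small. For four scores no bound can be given: section 2.4 does not say which state its figures describe, so at least one state has no stated power.

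**The case against.** The first sentence of 2.6.1 is a clear definition, and the second can be read as describing only how dyspnea is assessed; section 2.6.2.6 likewise has both scales recorded before and after the walk. This is a fair reading of 2.6.1, but the Abstract includes rest in the primary outcome itself, and the choice between Borg and VAS stays open either way.

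A multiplicity rule is commonly left to an analysis plan, and none is shown here. That stands: the lack of an alpha split or testing order in a condensed article is not a fault in itself. An analysis plan could not make the Abstract agree with 2.6.1, however.

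A reader might infer that the trial has four primary endpoints, that any one of them suffices, and that the false-positive rate is therefore two to four times 5%. The documents do not support this. Four is one of two readings. No any-one-suffices rule is written; 2.8 gives a general threshold, not a decision rule. The upper end needs independent scores, which is implausible for two breathlessness scales in the same patients.

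A reader might also suppose that resting scores will sit near zero because 2.2.2 sets no minimum dyspnea for entry. The article gives no resting values, so that is conjecture and nothing here rests on it.

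**Conclusion.** The point holds as an inconsistency that leaves the deciding endpoint unsettled. The contradiction between the Abstract and 2.6.1 is certain and needs no assumption. The inflation is conditional: about 7-10% for two scores or 9-19% for four if any one significant score is enough, over assumed correlations of 0.9 down to 0 and two-sided tests, with the upper ends unlikely. It is nil if all must succeed, in which case the 0.95 and 0.97 in section 2.4 are not the power for the trial's conclusion. It should be corrected, because the choice determines what result counts as positive.

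**What to change.** Name one scale and one state at week 8 as the sole primary endpoint, compared between groups by analysis of covariance adjusted for the baseline score. Post-walk VAS is the best anchored choice: the total of 90 comes from the VAS calculation in 2.4, and the post-walk state from the first sentence of 2.6.1. The two anchors are separate, since 2.4 does not say in which state its VAS was measured, and the revised text should say so. Test post-walk Borg at 0.05 only if the VAS is significant, and make both resting scores secondary.

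Two alternatives would also serve:
- **Co-primary scores that must all succeed**, with power restated for joint success.
- **An alpha split**: 0.025 each for two scores (4.94% overall if independent) or 0.0125 each for four (4.91%). As an illustration only, assume a two-sample t-test with 39 per arm and 95% power at 0.05 (standardised difference about 0.83). Power would then be about 91% at 0.025 and 86% at 0.0125. Section 2.4 reports a paired-means calculation, so these figures are not the plan's own.

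Align the Abstract, 2.4 and 2.6.1 before any unblinded data are seen. The registry entry is not among the documents, so whether it needs the same change should be checked. The cost is wording; the downside of the preferred option is that Borg or resting scores alone can no longer carry the efficacy claim.

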##### 2.6.1.1 Borg Dyspnea Scale

The Borg Dyspnea Scale is a modified Borg scale of perceived exertion appropriate for measuring dyspnea (31).

##### 2.6.1.2 VAS

The VAS is a line ranging from 0 (indicating no breathlessness) to 10 (indicating the most severe breathlessness imaginable), which represents the severity of dyspnea in increments of 1 cm (32).

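### The VAS, a primary instrument, is described in 1 cm increments; reading the mark to 1 mm would keep precision at almost no cost, though the loss is small unless resting scores are low and narrow

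*Protocol article*

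**What the plan says.** Section 2.6.1.2 defines the instrument and states its resolution: it is a line "which represents the severity of dyspnea in increments of 1 cm", running from 0 for none to 10 for the worst breathlessness the patient can imagine. The article mentions no millimetre reading anywhere.

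The VAS is a primary instrument. The Abstract (Methods) gives the primary outcome as dyspnea severity "as measured using the Borg Dyspnea Scale and a visual analog scale at rest and after exercise". Section 2.6.1 opens more narrowly, "The primary outcome is the severity of dyspnea measured after the 6-min walking test (6MWT"), and then adds: "The severity of dyspnea at rest and exertional dyspnea after 6MWT will be assessed using the Borg Dyspnea Scale and a VAS".

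The VAS also sets the size of the trial. Section 2.4 states: "The sample size calculation was based on the dyspnea visual analog scale (VAS) score". It reports that "a total of 78 patients with stable COPD should be included in the study to achieve a statistical power of 0.95", which is then raised to 45 per group. The separate calculation on the Borg scale would need only 16 patients. Section 2.8 compares the groups by analysis of covariance, so the VAS is handled as a quantitative score.

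**The concern.** A mark placed freely on a 10 cm line can be measured to the millimetre. If it is recorded in whole centimetres, 0.6 and 1.4 both become 1, while 1.4 and 1.6 become 1 and 2. The recorded score then carries rounding error at baseline and again at week 8. That error enters the residual variance of the between-group comparison and brings nothing in return.

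What is at stake is precision on a primary measure. The proportional cost grows as the spread of true scores shrinks, so it depends on which state is measured. A widely spread post-exercise score would lose little, and a resting score bunched near the floor would lose more.

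**Working it through.** **The plan's own figure.** The 78 evaluable patients cannot be reproduced, because section 2.4 gives neither the VAS difference nor its SD. As a benchmark I solved back for the effect that gives 95% power at two-sided 5% (sidedness is assumed) with 39 per arm in a two-sample comparison. The result is a standardized difference of 0.83. Section 2.4 itself names a different procedure ("The test for paired means in PASS software version 15.0.5"), so 0.83 is only a reference point for between-group power.

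**Added variance.** Rounding to a step h adds about h²/12:
- 1 cm: 1/12 = 0.083 cm², an added SD of 0.289 cm.
- 1 mm: 0.01/12 = 0.00083 cm², which is negligible.

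**Effect on a baseline-adjusted comparison.** The assumptions are that baseline is the covariate (section 2.8 does not name it), that SD s is the same at both visits, and that the correlation is r = 0.6. Write v = s² + 1/12. Then:
- residual variance without rounding = s²(1 − r²) = 0.64s²
- residual variance with 1 cm rounding = v − (0.6s²)²/v

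For s = 2: v = 4.0833, so 4.0833 − 2.4²/4.0833 = 2.673. Against 0.64 × 4 = 2.56, the ratio is 1.044.

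For s = 1.5: v = 2.3333, so 2.3333 − 1.35²/2.3333 = 1.552. Against 1.44, the ratio is 1.078.

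The formula ignores the floor at 0, so I also simulated 400,000 baseline/week-8 pairs per case, limited to 0–10 and rounded to 0.1 or to 1. The sample-equivalent loss is 1 − 1/ratio. Power is for 39 per arm, starting from 95.0%. All means and SDs are assumptions.

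| Assumed score | Variance ratio, 1 cm vs 1 mm | Sample-equivalent loss | Power |
|---|---|---|---|
| Post-6MWT, mean 5, SD 2 | about 1.045 | about 4% | about 94% |
| Post-6MWT, mean 5, SD 1.5 | 1.08 | about 7% | 93.5% |
| Rest, mean 2, SD 2 | 1.055 | about 5% | about 94% |
| Rest, mean 2, SD 1.5 | 1.09 | about 8% | about 93% |
| Rest, mean 1, SD 1 | 1.22 | about 18% | about 90% |
| Rest, mean 0.7, SD 0.6 | 1.58 | about 37% | about 82% |

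**Without baseline adjustment.** The rounding variance is then compared with the full score variance, so the proportional loss is smaller. It is 0.0833/4 = 2.1% for SD 2, 3.7% for SD 1.5, 8.3% for SD 1 and 33.3% for SD 0.5. Simulated two-sample power, 1 mm versus 1 cm, is:
- 94.7% vs 94.3% (mean 5, SD 2)
- 95.0% vs 94.3% (mean 5, SD 1.5)
- 92.3% vs 89.4% (mean 1, SD 1)
- 92.1% vs 80.7% (mean 0.5, SD 0.5)

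**Effect on the mean difference.** Simulated group differences, 1 mm versus 1 cm, are 0.496 vs 0.496 (mean 5, SD 2), 0.385 vs 0.390 (mean 1, SD 1) and 0.245 vs 0.255 (mean 0.7, SD 0.6). The cost is in variance. The difference itself is retained.

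**The case against.** The strongest objection is that section 2.6.1.2 is a one-sentence description of an instrument and not a scoring instruction. The 1 cm phrase may describe graduations printed on the line, and nothing says that a patient's mark is rounded. This stands as a genuine ambiguity. It does not remove the point: 1 cm is the only resolution the article states, the wording permits whole-centimetre scoring, and three centres could read it differently.

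A second objection is that a finer value may not exist. If patients choose a whole number on a graduated line, re-measuring completed forms recovers nothing. This stands, and it limits what can be done for participants already assessed.

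A third is that the loss hardly matters for the outcome named first in section 2.6.1, dyspnea after the 6MWT. This also stands: under the assumptions above, power falls from 95% to about 94%.

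A reader might go further and infer that resting scores sit near zero, so that rest-state precision is certainly poor. The article gives no VAS distribution in either state, and it enrols moderate-to-very-severe obstruction, so the 18–37% range is only a possibility. A reader might also infer that changes below 1 cm vanish. For a group comparison they do not, because the mean differences came through rounding essentially unchanged.

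**Conclusion.** The point holds as a minor measurement improvement. Section 2.6.1.2 states a coarse resolution for a primary instrument, and a millimetre reading can only add precision.

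With r = 0.6 and baseline adjustment assumed, the loss is about 4–7% of the sample after exercise. At rest it is about 5–8% if the mean is 2 with SD 1.5–2, and about 18–37% only if resting scores are both low and narrow. The resting figures bear on the primary outcome as the Abstract defines it. The opening sentence of section 2.6.1 names only the post-6MWT score.

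It would be tempting to conclude that the 90-participant sample is too small. The documents do not support that. The VAS difference and SD behind the 78 are not given, and if the source study scored in whole centimetres, its SD already contains the rounding variance.

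**What to change.** In section 2.6.1.2, state that the patient places a mark freely on a 10 cm line, that the mark is measured to the nearest 1 mm at all three centres, and that this value is the one analysed. For forms already completed, re-measure only where freely placed marks on paper exist.

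The cost is a short addition to the text, a ruler and slightly more care at data entry. No visit or procedure is added. The one real drawback is that resolution may be mixed if some participants have already been scored in whole centimetres and cannot be re-measured. In that case the recording rule used for each participant should be documented.

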#### 2.6.2 Secondary outcomes

##### 2.6.2.1 Modified Medical Research Council Dyspnea Scale

The modified Medical Research Council Dyspnea Scale is a 5-point (0–4) questionnaire developed to measure breathlessness; its score relates well to other multidimensional health status measures (33).

##### 2.6.2.2 Multidimensional instruments for dyspnea measurement

Dyspnea-12, a multidimensional measurement method, is composed of 12 dyspnea descriptors that can adequately reflect the physical and emotional aspects of dyspnea and its perception, offering a reliable evaluation of its severity (34).

